## Abstract

**Background:**

Despite the increasing options for public and private health care providers in the Lao People’s Democratic Republic (Lao PDR), choosing a high-quality provider or facility is difficult because timely and reliable information about providers is not readily available. Additionally, only 28% described their most recent visit to a health care provider as high quality, suggesting that while options for care are expanding, people may need support in finding providers that meet their quality needs. To inform efforts to improve access to high-quality care, evidence is needed on mechanisms that empower people to identify and use such care. The rapid adoption of mobile phones in Lao PDR, particularly in urban areas, offers opportunities to enhance access to timely, reliable information about health care facilities.

**Objective:**

This study aims to conduct an unblinded randomized controlled experiment using mobile phones to study whether routinely collected information on quality of care can improve access to high-quality care and patient satisfaction.

**Methods:**

Mothers with at least one child under 2 years of age who are already enrolled in the Vientiane Multigenerational Birth Cohort (VITERBI) will be invited to participate during in-person visits by the research staff. Participants will be randomly assigned in equal numbers to the control and intervention groups. The intervention group will receive a URL with facility ratings for pediatric health care services every 2 weeks via WhatsApp; the control group will not receive any messages. WhatsApp will also be used to administer biweekly surveys to both groups to assess the quality of care received in the past 2 weeks. The web page shared with the intervention group will display results from these surveys and from the pilot study. Research staff will conduct baseline and endline surveys with all participants during in-person visits, 3 months apart.

**Results:**

The trial is currently underway and scheduled for completion in 2025.

**Conclusions:**

This study will use a demand-side intervention to increase demand for high-quality child health care among mothers in Vientiane Capital. We will assess whether information on the quality of health care facilities—generated by study participants during the study period—influences mothers to change their preferred providers for nonurgent conditions.

**Trial Registration:**

ClinicalTrials.gov NCT06304831; https://www.clinicaltrials.gov/study/NCT06304831

**International Registered Report Identifier (IRRID):**

DERR1-10.2196/66085

## Introduction

While access to health care is expanding globally, there is appreciable variation in quality among providers, with low-quality care accounting for up to 5 million deaths each year [1]. These numbers are expected to grow as more people seek care and as the burden of disease shifts to complex conditions. Expanding access has also increased the options for public and private health care providers. Selecting a provider or facility, however, is difficult because timely and reliable information about providers is not readily available. In the Lao People’s Democratic Republic (Lao PDR), only 28% of people describe their recent visit to a health care provider as high quality [2], suggesting that while options for care are increasing, people may need support to find providers that meet their quality needs.

In order to inform efforts to improve people’s access to high-quality care, there is a need for evidence on mechanisms that empower people to identify and use such care. In low- and middle-income countries, the majority of efforts to date have focused on supply-side measures, such as enhancing the availability of medicines and equipment, introducing financing mechanisms that promote quality care, and strengthening the clinical competencies of health workers [1,3]. However, generating greater demand for health system quality is a key element of quality improvement strategies in low- and middle-income countries [4]. While there are new initiatives to study population perspectives and people’s care experiences, measures to “ignite demand” for high-quality care remain poorly understood.

Patients often face significant information asymmetry due to their lack of medical expertise, which prevents them from accurately assessing the quality of care they receive. This asymmetry, coupled with a lack of information about the quality of health care providers, results in suboptimal health care decisions and forces patients to rely on word of mouth or the reputation of providers [5]. Empirical evidence suggests that quality metrics can influence patient choices [6,7]. Additionally, recent studies have shown that online reviews can affect the selection of health care providers [8,9]. Therefore, given the large variation in the quality of care in low-resource settings [10,11], providing quality information can empower patients to make better-informed decisions about their health care.

We plan to conduct a randomized controlled experiment using mobile phones to study whether routinely collected information on quality of care can improve access to high-quality care and patient satisfaction. Specifically, we will examine whether participants switched providers—as a measure of improved access to quality care—based on the information provided, and whether such information led women to be more satisfied with the health care services received for their child or children. The rationale for the study is that access to the intervention (user ratings of health care facilities) can influence where caregivers seek care for their children. By providing information to caregivers across multiple quality domains that matter to users (ie, provider skill, provider respectfulness, cost, waiting time, staff helpfulness, and cleanliness), the intervention is intended to increase caregivers’ awareness of differences in quality and empower them to make more informed choices. We hypothesize that this increased awareness may lead to switching to better-rated facilities, particularly for nonurgent conditions—the study’s primary outcome. Additionally, making a more informed choice may result in greater satisfaction with the care received, due either to actual improvements in service quality or to closer alignment between expectations and experiences.

To explore these pathways, we include secondary outcomes that capture reported use of the ratings website, its perceived influence on facility selection, caregiver confidence in decision-making, and perceived quality of care. These measures will help us interpret the mechanisms through which the intervention may affect the primary outcome.

Study participants will include mothers living in 2 urban districts in Vientiane, the capital city, who have children under 2 years of age and are already enrolled in an ongoing Vientiane Multigenerational Birth Cohort (VITERBI), which includes the entire population of children born in the past 2 years in the study districts.

## Methods

### Participants and Randomization

This study consists of a randomized controlled experiment involving 660 mothers with children under 2 years of age from an ongoing VITERBI study, which includes the local population of young mothers in 4 districts of Vientiane Capital. Mothers with at least one child under 2 years old, already enrolled in the VITERBI study and living in 1 of 2 urban districts (Sikhottabong or Chanthabouly), will be invited to participate in the study during in-person visits by the research staff. We will use rolling enrollment while ensuring that each participant is enrolled in the study for a maximum of 3 months. Participants will be randomly assigned to 1 of 2 groups: (1) a control group that will not receive any information about providers, and (2) an intervention group that will receive biweekly updates on quality ratings based on reviews collected from mothers of young children in the study areas. The unit of randomization will be the individual participant. A simple random number draw, generated by the Open Data Kit (ODK) package installed on the tablets, will be used to assign participants to treatment or control with equal probability.

Research staff will administer baseline (see Multimedia Appendix 1) and endline (see Multimedia Appendix 2) surveys to all participants during in-person visits held 3 months apart. Responses to these surveys will be used to measure the study’s primary outcome: the proportion of mothers who changed their preferred health care facility for nonurgent child care services between the 2 surveys. This outcome assesses whether information about health care providers can influence users to seek alternative sources of care. For a completed CONSORT-EHEALTH (Consolidated Standards of Reporting Trials of Electronic and Mobile Health Applications and Online Telehealth) checklist, see Multimedia Appendix 3.

### Selection of Participants

#### Inclusion Criteria

All women aged 18 years or older, enrolled in the VITERBI study with at least one child under 2 years of age, living in 1 of 2 urban districts (Sikhottabong or Chanthabouly), able to read, having exclusive access to a mobile phone, possessing a WhatsApp (Meta Platforms, Inc) account, and able to understand and sign the informed consent form will be eligible to participate in the study (see Multimedia Appendix 4). The eligibility criteria will be assessed using data collected from the VITERBI study. Ability to read will be tested using the Lao script: “I use my mobile phone every day.” Before the study, we conducted interviews with 35 randomly selected women enrolled in the VITERBI study to gain insights into mobile phone ownership and usage. We found that 33 out of 35 (94%) owned a smartphone, and among these owners, all used the WhatsApp messaging app to send or receive messages and to make calls. Therefore, we limited the eligibility criteria in the main study to VITERBI participants with access to a smartphone and an existing WhatsApp account.

#### Exclusion Criteria

Women who are unwilling to sign informed consent, are under 18 years of age, do not have access to a smartphone, are unable to read the test script, or are unable to operate a smartphone will be excluded from the study.

### Study Preparation Procedures

#### Overview

There were 3 preparatory phases leading up to the pilot. Phase 1 involved a preliminary survey of smartphone ownership and use among 36 randomly selected participants in the VITERBI study. In phase 2, we conducted cognitive interviews with 5 women to ensure the understandability of the baseline and endline questionnaires, and we tested both the understandability and usability of the website design prototypes. In phase 3, we conducted a pilot study with 68 participants to test the study procedures. The final phase involved conducting the main study.

#### Phase 1: Mobile Phone Ownership and Website Development

We conducted a preliminary survey to assess mobile phone ownership among VITERBI participants, usage frequency, and the types of software used for communication. This survey included 36 randomly selected mothers from the VITERBI study residing in 2 urban districts (Sikhottabong and Chanthabouly). Given that the sample resided in the urban core of Vientiane Capital, 33 out of 35 (94%) owned smartphones, and among these owners, all were regular WhatsApp users.

The website’s design was informed by qualitative interviews with 13 randomly selected VITERBI participants, 23 exit interviews with women at 6 public hospitals, and additional study volunteers. We used a predefined interview guide to qualitatively assess, interpret, and analyze several prototypes consisting of facility rating summaries and detailed web pages of individual health facilities. To gather additional feedback, we conducted exit interviews with mothers at the same 6 major public hospitals. These hospitals were ideal locations to test the intuitiveness and interpretation of ratings, as they also serve women from remote or rural areas who may face literacy challenges, unlike the highly educated women in the VITERBI study. The qualitative interviews revealed that mothers were familiar with ratings or scores; 1 participant described it as “similar to a score for exams in school.” Women were generally glad to receive information about health care providers for their children. There was a clear preference for using stars to represent the overall average score, and several women requested that phone numbers be displayed to help them contact health facilities. The prototypes selected for the study, shown in Figures 1 and 2, were the most favored and easily understood by the women.

The website was developed by Young Innovations, Private Limited, based in Lalitpur, Nepal, and procured by the study’s sponsor. The website and the data generated by study participants through their ratings of health facilities are jointly owned by the study’s sponsor and Lao Tropical and Public Health Institute.

**Figure 1 figure1:**
[figure not shown]
Home page of the website (intervention).

**Figure 2 figure2:**
[figure not shown]
Second page of the website (intervention).

#### Phase 2: Development of the Survey Questionnaire and Cognitive Interviews

Before the fieldwork in Laos, we developed baseline and endline survey questionnaires to measure primary and secondary outcomes, along with other relevant indicators. Measures of parental health literacy, parental confidence in navigating the health system, and parental confidence in interactions with health care providers were adapted from the Consumer Health Activation Index [12]. Measures related to sick children were adapted from the Integrated Management of Childhood Illnesses [13]. Additionally, measures on care utilization, care experience, expectations for health care quality, and quality of care were adapted from the People’s Voice Survey [14], which had previously been implemented in Laos in 2022 [2]. Once finalized, cognitive interviews were conducted with 5 VITERBI participants in Lao-Tai, the official language, using a combination of the “think-aloud” and “scripted probing” techniques [15]. These interviews helped identify suitable terminology for concepts such as parental health literacy, health system navigation, and confidence in interactions with care providers.

The primary outcome of the study will be based on participants’ responses to the following question, asked in both the baseline and endline surveys: “If your child is sick tomorrow with a mild fever of 38°C and cough, which hospital, clinic, or health center will you take your child to?” This question was developed in accordance with the Integrated Management of Childhood Illness guidelines [13], in which the described symptoms would be classified as nonsevere. We developed this measure specifically for this trial, guided by our theory of how the intervention might influence decision-making. We aimed to create a measure that captured intentions about where participants would seek care in a future scenario, as we anticipated that the information provided through the intervention could shape these intentions. We sought an outcome measure that could be collected from all participants without depending on recent health care utilization. For this reason, we chose this measure over alternatives such as “most recent facility visited” or “usual source of care.” Cognitive interviews and pilot surveys indicated that the measure performed well in terms of participant comprehension.

#### Phase 3: Pilot Study

We conducted a pilot study to assess the study procedures and gather feedback on the intervention and questionnaire. For the pilot’s endline survey, we added qualitative questions to capture participants’ suggestions for improving the website. Based on pilot results, we made minor revisions to the baseline and endline survey questions to enhance clarity. We also refined the quality components to overall quality, skill and experience of the health care provider, equipment, respectfulness of the health care provider, cleanliness, waiting time, and cost.

### Study Procedures

Research staff, with support from the respective village offices, will recruit participants during in-person visits. At the first meeting, before enrollment and the baseline survey, research staff will explain the study and obtain informed consent. The informed consent will cover key information, including the study’s objectives, duration, level of participant involvement, and the assurance that participation is entirely voluntary. Tablets equipped with ODK will be used to record responses from enrolled participants during the baseline and endline surveys. All participants will receive a small gift in appreciation of their participation, in keeping with customary practice in Lao PDR.

After completing the baseline survey, research staff will assist all enrolled participants in connecting with the study’s WhatsApp number and will demonstrate how to submit biweekly user ratings of facilities. In addition, staff will encourage participants in the intervention group to use the website, as needed, to access information on pediatric health care facilities and view user ratings submitted by their peers. Research staff will demonstrate the 3 main pages of the website, show participants how to navigate between them, and answer any questions they may have. The study coordinator will record enrolled participants weekly, along with their group assignment (intervention or control), and will schedule dates for each participant to receive biweekly surveys, the intervention URL (for those in the intervention group), and the endline interview.

Following enrollment, all participants will be asked to rate or review the most recently visited health care facility every 2 weeks; these ratings will generate user scores for the website (intervention). Participants will receive a WhatsApp message from the study coordinator: “Did you visit a health center, hospital, or clinic for your child in the last 2 weeks?” Those who respond “yes” will receive a URL to a web-based survey, along with their study ID and the last 4 digits of their phone number. Before completing the survey, participants will be required to enter their study ID and the last 4 digits of their phone number. This step will help track survey completions and identify duplicate entries. Once the 2 fields are entered, participants will be asked to complete the survey by identifying the name of the health facility visited, rating the quality of care received, and providing any additional comments about their visit. The questions in the web-based survey are adapted from the People’s Voice Survey questionnaire [16], a mobile-based tool designed to capture patient experiences. All questions use multiple-choice response options and focus on participants’ most recent visit to a health care facility within the past 2 weeks. Participants are asked to assess the quality of care their child received by responding to the following items:

How would you rate the overall quality of care your child received?How would you rate the knowledge and skills of your provider?How would you rate the equipment and supplies available to the provider, such as medical equipment or access to laboratory tests?How would you rate the level of respect your provider showed you?How would you rate the amount of time you waited before being seen?How would you rate the courtesy and helpfulness of the health care facility staff, excluding your provider?How would you rate the cost of services?How would you rate the cleanliness of the facility?

For each question, participants will select one of the following response options: excellent, very good, good, fair, poor, “I do not know,” or “I refuse to answer.”

The principal investigator will monitor survey entries weekly to ensure completeness and identify duplicate entries. In the case of duplicates, the most recent entry will be retained. If participants do not respond to the initial WhatsApp message or fail to complete the mobile survey, the study coordinator will make up to 5 attempts to contact them via WhatsApp and administer the survey over the call.

Average ratings for overall quality of care and for specific dimensions of care will be displayed on the web page, which is the main component of the intervention. The study coordinator will share the URL of the health facility ratings website with the intervention group biweekly via WhatsApp. The message will read: “Sabaidee, please click on the link to see ratings of hospitals, clinics, or health centers for health care for your children, and let us know if you have any questions or comments.” The control group will not receive any intervention. Given that all participants in the pilot study exchanged WhatsApp messages at least once per month, biweekly sharing of the intervention URL over 3 months is expected to provide sufficient exposure to the website for participants in the intervention group. Research staff will conduct endline surveys with all participants during in-person visits 3 months after the baseline survey.

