### Data Management

Survey data will be recorded using unique identifiers for each participant. An enrollment log will be maintained to link these codes with participants’ phone numbers and will be used solely for study administration. Responses to the baseline, endline, and mobile-based surveys will be stored electronically using only the individual codes, without any phone numbers.

AA and a research coordinator will maintain the enrollment logs electronically on a password-protected, secure Swiss TPH server that will be regularly backed up. The enrollment log will be saved using the following format to ensure traceability of any changes: LaosMR_enrol_v1.0_DD.MM.YYYY. The research team (AA, GF, and [name]) will have access to password-protected survey responses from the baseline, endline, and mobile phone surveys.

Data collected during the biweekly surveys will be stored on a password-protected cloud server, accessible only to the research team (AA, GF, and [name]). Hard copies containing participant information will be kept in a locked filing cabinet in the project office at the Lao Tropical and Public Health Institute. These files will be accessible only to the local study coordinator and enumerators responsible for conducting the baseline and endline surveys.

We will use WhatsApp for 2 main purposes: (1) to ask all participants whether they have visited a health care facility for their children in the past 2 weeks and, if they respond affirmatively, to send them a link to an online survey to rate the quality of care they received; and (2) to provide the intervention group with a URL link to the website displaying user ratings of health facilities for pediatric care. The local study coordinator will communicate with participants using a dedicated tablet and a unique WhatsApp account, used exclusively for the study. The tablet will be password-protected and accessible only to the local study coordinator. Messages exchanged between participants and the study coordinator on WhatsApp are secured with end-to-end encryption [17]. At the conclusion of the study, all contacts will be deleted, and the WhatsApp account will be disabled.

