### Limitations

This protocol also has some limitations. First, the study may inadvertently encourage bypassing of lower-level public health facilities, directing mothers toward specialty hospitals or private providers. A recent study showed that a large majority (64%) of people used public hospitals as their preferred health care provider, while only 13% used health centers [20]. As a consequence of the study, government-managed specialty hospitals and private facilities may experience increased demand for services for minor health conditions that could be better managed at lower-level government facilities. This shift toward private and specialty providers could raise out-of-pocket expenditures for health care clients and increase costs for the health system as a whole. Second, the quality of care measures used in the study are based on participants’ perceptions and may be influenced by social desirability bias. However, previous studies have shown that people in Lao PDR are highly critical of health system performance [2,21]. Third, nonadherence to the intervention due to unexpected events—such as technical issues with the website or not receiving the URL—may also bias study findings. To address this, we will assess participants’ frequency of website use in the endline survey and document any website-related downtime. Fourth, because all participants reside in the same 2 districts and the study uses an open-label design, cross-arm exposure and spillover effects may bias the results. To minimize these risks, we have separated the roles of staff: the team member responsible for communicating with the intervention group (sending biweekly reminders and links to the ratings website) is not involved in scheduling or conducting endline surveys or other administrative assessment activities. Additionally, to assess aggregate exposure, we will track daily traffic to the website. To measure exposure at the individual level, all participants will be asked at endline about their knowledge of the intervention, whether they received the link, how they received it, and how frequently they accessed the website. Finally, the researcher responsible for data analysis will also be involved in data collection; therefore, complete blinding of the analyst is not possible. In practice, however, the analyst will remain blinded during the endline assessments.

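### The Limitations section says the person who sends the ratings link does not schedule endline surveys, but Study Procedures gives both tasks to the study coordinator, who also records each mother's arm

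*Protocol article*

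**What the plan says.** The Limitations section of the protocol article names cross-arm exposure, spillover and the open-label design as possible sources of bias, and offers separation of staff roles as the protection. The role set apart is "the team member responsible for communicating with the intervention group (sending biweekly reminders and links to the ratings website"). That person, it says, "is not involved in scheduling or conducting endline surveys or other administrative assessment activities".

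The Methods assign the tasks as follows.

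- Sending the link (Study Procedures): "The study coordinator will share the URL of the health facility ratings website with the intervention group biweekly via WhatsApp".
- Recording the arm (Study Procedures): "The study coordinator will record enrolled participants weekly, along with their group assignment (intervention or control").
- Scheduling endline: the same sentence, with the same subject, goes on to say that the coordinator "will schedule dates for each participant to receive biweekly surveys, the intervention URL (for those in the intervention group), and the endline interview".
- Holding the messaging device (Data Management, on the dedicated WhatsApp tablet): "The tablet will be password-protected and accessible only to the local study coordinator".
- Conducting endline (Study Procedures): "Research staff will conduct endline surveys with all participants during in-person visits 3 months after the baseline survey".

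**The concern.** The safeguard and the procedures describe different trials. In Limitations, whoever is in regular contact with the intervention arm has no hand in arranging the outcome visit. In Study Procedures, that person arranges it, with the arm on record.

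This matters because of how the primary outcome is built. It is a yes/no indicator of whether the stated preferred facility differs between baseline and endline (Outcomes), and participants without outcome data are excluded with no imputation of outcomes (Statistical Analysis). The estimate therefore depends on who is seen at endline and may depend on how long after baseline they are seen. A scheduler who knows the arm, and who has additional link-related contact with one arm only, could influence either without meaning to. If the procedures are the true account, readers of the results would be told of a protection that the trial did not have.

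**Working it through.** The point concerns staff roles and depends on no alpha, power or effect size. The check is to set the sections side by side.

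| Task | Limitations | Methods |
|---|---|---|
| Send ratings link | One team member, kept separate | Study coordinator (Study Procedures) |
| Record arm | Not mentioned | Study coordinator (Study Procedures) |
| Schedule endline | Not the link sender | Study coordinator (Study Procedures) |
| Conduct endline | Not the link sender | Research staff (Participants and Randomization; Study Procedures) |

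1. **Is it the same role?** Study Procedures uses the same title for sending the link and for scheduling endline. Data Management also refers to a local study coordinator and a research coordinator, so two people might exist in practice, but no section divides these duties between them.

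2. **Could someone else send the link?** Not as written. Messages to participants go out from a dedicated WhatsApp tablet that only the local study coordinator can use. The ODK tablets used for the in-person surveys are a separate matter.

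3. **Which parts of the safeguard fail?** On scheduling, the two accounts conflict directly. On conducting endline, they do not: no section gives the interviews to the coordinator. On other assessment work, the conflict is arguable. For mothers who do not answer the biweekly survey, "the study coordinator will make up to 5 attempts to contact them via WhatsApp and administer the survey over the call". Whether that counts as an administrative assessment activity is a matter of reading, and the point does not need it.

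4. **Is there room for an effect?** The plan enrolls 660 and anticipates 600 endline surveys, so 660 − 600 = 60 mothers, or 60/660 = 9.1%, are expected to have no outcome. The document gives no expected split of these by arm, no relation between being missed and changing facility, and no expected spread of endline dates. The direction and size of a bias cannot be calculated from it.

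**The case against.** The strongest reply is that scheduling may leave little to discretion. Endline is set at 3 months after baseline, participation is limited to 12 weeks, and the principal investigator monitors enrollment logs and survey progress. On that reading, the coordinator merely enters predetermined dates in a calendar, and a systematic lag in one arm would depart from the plan. This stands as a reason not to assume that harm occurred. It does not remove the contradiction, because the Limitations section denies any involvement of the link sender in scheduling.

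A reader might also infer three stronger things that the document does not support.

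- **That no separation exists at all.** The interviews belong to research staff, and Data Management likewise refers to enumerators conducting the surveys. That half of the safeguard is not contradicted.
- **That the coordinator also pursues mothers for the endline visit.** The repeated contact attempts in Study Procedures and the calls in Attrition concern the biweekly surveys, which go to both arms. The attempts described under Interim Analysis and Stopping Guidelines belong to the study team. No section says who follows up missed endline visits.
- **That the type I error is inflated by a stated amount.** Any such figure needs an assumed follow-up gap between arms, an assumed difference in switching among missed mothers, or an assumed lag in visit dates with a model for how switching builds up. A steady accrual model is doubtful here: the outcome compares two stated preferences, a mother can switch back, and the pilot's 45% was seen over 6 weeks.

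Visit windows and contact rules may sit in the full protocol, and their absence from the article is not criticized.

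**Conclusion.** The protocol article is wrong as written on one specific matter. Limitations claims that the link sender does not schedule endline, and Study Procedures assigns both tasks, with the recording of arm, to the study coordinator. This rests on reading the coordinator in Study Procedures as one role, which the shared title and the restricted tablet support. If two people in fact share the work, the text needs to say so.

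The consequence is a possible influence on the timing and completeness of the primary outcome, of unknown size and direction. The outcome definition, the primary test and the sample size are unaffected.

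**What to change.** 1. State who schedules the endline interview, and make Study Procedures, Data Management and Limitations agree.
2. Have each endline due date generated automatically from the baseline date by the same rule in both arms. Alternatively, assign scheduling to an existing staff member who neither sends links nor holds the allocation list. Handing it to the enumerators does not by itself secure this: research staff demonstrate the website to intervention mothers after baseline, and enumerators conduct both surveys, so they may already know the arm.
3. Report days from baseline to endline, and endline completion, by arm.
4. The trial is under way. If the coordinator has already been scheduling endline visits, correct Limitations so that it no longer claims this separation.

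The cost is a wording change, a date rule or the reassignment of one task, and two descriptive summaries from visit dates and completion records that the trial should already hold. For mothers already seen, only the correction and the reporting can still be done.
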